## Abstract

**Background:**

Social anxiety disorder (SAD) is characterized by a marked fear of negative evaluation in social situations and significant impairments. Even with the most effective treatments, remission rates are around 50%. An important reason for the limited effectiveness of treatments is the lack of evidence-based explanation of how treatments work and what their active ingredients might be. An approach to unpack the active ingredients and mechanisms of treatment is the factorial design.

**Objectives:**

The study is a factorial trial aiming (1) to examine the main effects and interactions for the four main treatment components of internet-based cognitive-behavioral therapy (ICBT) for SAD (i.e., psychoeducation, cognitive restructuring, attentional training, and exposure) and (2) to examine whether and which change mechanisms mediate the relationship between treatment components and symptom reduction.

**Methods:**

A total of 464 adults diagnosed with SAD will be randomized to one of 16 conditions containing combinations of the treatment components. The primary endpoint is SAD symptomatology at eight weeks. Secondary endpoints include symptoms of depression and anxiety, quality of life, and negative effects. Hypothesized change mechanisms are the increase of knowledge about SAD, the decrease of dysfunctional cognitions, the decrease of self-focused attention, and the decrease of avoidance and safety behaviors.

**Discussion:**

A better understanding of the differential efficacy of treatment components and mechanisms of treatment underlying ICBT for SAD might inform clinicians and researchers to plan more potent and scalable treatments.

**Trial registration:**

clinicaltrials.gov (NCT04879641) on June, 11th 2021. https://clinicaltrials.gov/ct2/show/NCT04879641.

## Introduction

1

Social anxiety disorder (SAD) is characterized by a marked and persistent fear of negative evaluation in social situations (American Psychiatric Association, 2013) and is a prevalent and disabling disorder across the globe (Stein et al., 2017). Although effective treatments such as psychotherapy and pharmacotherapy are available, far from all individuals suffering from SAD seek and eventually find help (Dalrymple and Zimmerman, 2011). Internet interventions offer many potential benefits, such as providing broader and easier access to empirically supported treatments affordably and conveniently.

The efficacy of internet interventions such as guided self-help interventions has been demonstrated for a variety of mental disorders in many randomized controlled trials (RCTs) and meta-analyses (Andersson et al., 2014; Andersson et al., 2019b; Carlbring et al., 2018; Karyotaki et al., 2017). SAD is probably the disorder for which internet-based guided self-help treatments have the most robust empirical support (Hedman et al., 2016). In this treatment format, patients work their way through a structured self-help program, typically based on CBT manuals (Clark, 2001; Clark and Wells, 1995), and therapists (also referred to as coaches or guides) assist and support them via a secure e-mail system. Overall, the vast majority of the RCTs investigating such Internet-based cognitive-behavioral treatments (ICBT) for SAD reported substantial reductions of social anxiety symptoms (Andersson et al., 2019a; Boettcher et al., 2013) and cost-effectiveness (Hedman et al., 2011). However, and as with conventional face-to-face treatments (Loerinc et al., 2015), there is still much room for improving the efficacy of ICBT for SAD as a considerable number of patients do not recover fully after treatment. The number of participants fulfilling the criterion of clinically significant change (Jacobson and Truax, 1991) at the end of ICBT ranges between 36 and 56% across studies on ICBT for SAD (Boettcher et al., 2013).

An important reason for the limited efficacy of face-to-face and ICBT for SAD is the limited understanding of how these treatments work and what their active ingredients might be. Various reviews convincingly argued that the active ingredients of CBT need to be identified so that therapy can be made more efficacious and probably also briefer (e.g., Holmes et al., 2014; Kazdin, 2017). Identifying the active ingredients requires the use of rigorous study designs that test the presence or absence of individual therapeutic elements rather than conventional parallel-group randomized controlled trials (RCTs). Conventional RCTs are the gold standard for determining if the intervention package works by establishing the relative efficacy of one treatment intervention versus a control group (e.g., another treatment package, attention control, wait-list). However, RCTs have limitations in identifying active ingredients because they usually only compare the overall effect of an entire intervention package. Current evidence-based psychological treatments for SAD, such as CBT, are made of multiple components, including psychoeducation, cognitive restructuring, attention training, and exposure. Each of these treatment components can (a) contribute to a greater or lesser extent to the effect of the treatment package, (b) act via distinct mechanisms, and (c) act via synergistic or antagonistic interactions (Collins, 2018).

As for the specific case of SAD, little effort has been made to answer the question of the differential effects of treatment components in face-to-face settings. Evidence for differential effects of specific treatment components usually comes from underpowered clinical trials with little control over treatment integrity, and results are inconsistent (e.g., Hope et al., 1995; Mattick et al., 1989; Nortje and Posthumus, 2012). The most reliable evidence so far comes from meta-analyses, but the conclusions are still not consistent. For instance, Powers et al. (2008) found that cognitive and behavioral interventions for SAD combined were not significantly more effective than cognitive treatments alone or exposure treatments alone. Also, no significant differences were found in direct comparisons of cognitive techniques alone and exposure alone (Feske and Chambless, 1995; Gil et al., 2001; Powers et al., 2008). These findings conflict with other meta-analytic evidence showing that exposure-based interventions alone yielded the largest effect size, whether alone or combined with cognitive restructuring (Gould et al., 1997). Besides the discrepant findings, research has failed to look into the active components of treatments separately (Acarturk et al., 2009). Thus, it is unclear which intervention components work and which do not and which ones work particularly well together. In line with this, how or why well-studied interventions for SAD produce change is mostly unknown.

The factorial experiment is an efficient and economical way of studying the individual and combined effects of sets of intervention components (Collins et al., 2014; Watkins and Newbold, 2020). However, factorial designs are still rare in psychotherapy research. One of the reasons is that in traditional psychotherapy, it is challenging to clearly demarcate treatment components and avoid an unwanted drift from the treatment protocol by therapists. Standardization and the avoidance of spillover effects (e.g., avoiding therapists using techniques from other treatment components) are essential for a successful factorial experiment. With the advent of internet-delivered treatments, the possibility to successfully realize factorial designs has improved. In this new treatment format, the intervention content can be standardized, and treatment integrity (the degree to which an intervention is implemented as intended) can be controlled (Collins, 2018; Watkins et al., 2016).

Although adding a factor to a factorial experiment does not require the same relatively large increase of the number of participants as an additional treatment arm would require in an RCT (see below; Collins et al., 2014), factorial trials still need quite large sample sizes to have sufficient power. With internet interventions, it is much easier to conduct large trials than in conventional psychotherapy research, with some clinical trials with more than 1000 participants (e.g., Klein et al., 2016), which is one reason why this field has developed at a fast pace (Andersson, 2015). Due to the possibility to control the delivery of standardized treatment components and to run trials with large sample sizes, several research groups (including our own) have recently started to conduct factorial trials to identify the active ingredients of internet interventions (e.g., Berg et al., 2020b; Bur et al., 2021; Watkins et al., 2016). Factorial trials have also been recommended to understand the mechanisms of change because they “provide direct evidence about the effects and interactions of individual components within a treatment package” (Watkins and Newbold, 2020, p. 429).

### Objectives

1.1

The primary objective of this trial is to investigate the active ingredients of ICBT for SAD by testing the main effects and interactions for the four main treatment components (i.e., psychoeducation, cognitive restructuring, attention training, and exposure) on primary (i.e., decrease in social anxiety symptoms) and on secondary outcomes (i.e., decrease in depressive symptoms, decrease in general anxiety, increase of quality of life, and client satisfaction). Furthermore, we also aim to investigate the effects of each treatment component on hypothesized change mechanisms and explore whether and which change mechanisms mediate the effect of the treatment components on symptom reduction. The specific secondary objectives (1) to investigate whether the specific mechanisms (i.e., knowledge gain of SAD, decrease of dysfunctional social cognitions, decrease of self-focused attention, decrease of avoidance and safety behaviors) mediate the effect of the treatment components on primary and secondary outcomes, and (2) to address additional exploratory research questions, including examining the negative effects of the treatment components and potential moderators of treatment outcome.

## Methods

2

### Study design

2.1

The study is a single-center, block randomized, balanced factorial trial with four treatment components (experimental factors), each evaluated at two levels (presence vs absence), resulting in 16 conditions (2 × 2 × 2 × 2; see Table 1). Although there are 16 experimental conditions, this study should not be considered a 16-arm RCT (Collins, 2018). The purpose of the factorial experiment is not to compare the 16 conditions to each other but to estimate the main effects of the four treatment components and interactions between the components. Each estimation of the main effects and interactions is based on all the conditions and, therefore, on all participants. For example, the main effect of the cognitive restructuring component will be estimated by comparing the mean of the experimental conditions in which the cognitive restructuring component is present (5, 6, 7, 8, 13, 14, 15, 16 in Table 1) vs the mean of the experimental conditions, in which cognitive restructuring is absent (1, 2, 3, 4, 9, 10, 11, 12 in Table 1). To calculate a two-way interaction (i.e. effect of one component depending on the level of the other factor), one has to calculate the difference between the average effect of one component at the two levels of the other component (present vs absent) and then averaging over all other factors. For a detailed explanation, see Collins (2018).

**Table 1 t0005:** Experimental conditions of the factorial design, with the presence (yes) and absence (no) of each component.

Condition	Psychoeducation	Cognitive restructuring	Attention training	Exposure
1 WL	No	No	No	No
2	No	No	No	Yes
3	No	No	Yes	No
4	No	No	Yes	Yes
5	No	Yes	No	No
6	No	Yes	No	Yes
7	No	Yes	Yes	No
8	No	Yes	Yes	Yes
9	Yes	No	No	No
10	Yes	No	No	Yes
11	Yes	No	Yes	No
12	Yes	No	Yes	Yes
13	Yes	Yes	No	No
14	Yes	Yes	No	Yes
15	Yes	Yes	Yes	No
16 full	Yes	Yes	Yes	Yes

WL = Wait-list condition. For ethical reasons, participants randomized to condition 1 will be offered treatment after eight weeks.

### Participants

2.2

A total of 464 participants with a SAD diagnosis will be included in the study, with 29 participants each assigned to one of the 16 conditions. Participants who return the informed consent will be included in the study if they (1) are 18 years or older; (2) have access to the internet and to a smartphone, PC or tablet; (3) have sufficient knowledge of German; (4) exceed predefined cut-off scores out of two social anxiety measures (22 points on the Social Phobia Scale or 33 points on the Social Interaction Anxiety Scale; SPS & SIAS; German version: Stangier et al., 1999); (5) fulfill the diagnostic criteria of SAD according to a diagnostic telephone interview; (6) in the case of taking psychiatric medication, the treatment is stabilized over one month.

Candidates will be excluded from the study if they (1) score two or higher on the suicide item of the PHQ-9 or show active suicidal plans in the diagnostic telephone interview; (2) have other highly impairing comorbid psychiatric conditions (i.e., history of psychotic or bipolar disorder) and (3) undergo another psychological treatment at the beginning of the study.

### Recruitment

2.3

Participants will be recruited using reports in newspapers, flyers, through internet forums, social media (e.g., Facebook), via our study website (https://selfhelp1.psy.unibe.ch/shyne/homepage_interessierte) and our research hub website for internet interventions (http://www.online-therapy.ch/) in German-speaking countries. The link to the study website will also be publicized using Facebook Ads and the Google Ads tool.

### Treatment

2.4

The internet-based self-help program (Shyne) is based on the well-established cognitive-behavioral treatment for social anxiety disorder by Clark and Wells (1995). It has been proven efficacious in previous studies in our research hub (Berger et al., 2009, Berger et al., 2011; Schulz et al., 2016; Stolz et al., 2018) as well as in previous studies from other universities and countries (e.g., Boettcher et al., 2012; Chen et al., 2020; Kählke et al., 2019; Kishimoto et al., 2016; Lin et al., 2020). The Shyne program consists of the following four treatment components:1)*Psychoeducation*: This treatment module delivers (1) detailed evidence-based information on SAD with a focus on maintaining processes (e.g., the vicious cycle of negative thoughts and emotions, cognitions, and behaviors associated with the maintenance of SAD) and (2) a brief overview of the evidence-based CBT strategies to overcome SAD (i.e., psychoeducation about the principles behind cognitive restructuring, attention training and exposure). Additionally, participants are asked to write about their anxiety-inducing situations as well as thoughts, feelings and possible avoidance behaviors associated with the described situations. Participants are encouraged to develop an individual model of their social anxiety symptoms based on the information provided.2)*Cognitive restructuring*: In this treatment module, participants are instructed to identify and modify dysfunctional and negatively biased assumptions. It includes a thought diary to track negative beliefs in daily routine and exercises to formulate helpful and adaptive thoughts.3)*Attention training*: In this treatment module, participants are trained to reduce self-focused and biased attention. Audio, video and text-based exercises in which participants learn to intentionally direct the attention away from themselves (i.e., less private self-consciousness) and to be less alert to potentially dangerous external social stimuli (i.e., less public self-consciousness; Duval and Wicklund, 1972; Fenigstein et al., 1975).4)*Exposure*: In this treatment module, participants are instructed to plan and track in vivo exposures using an exposure diary. Participants are also advised to reduce safety behaviors, overt or covert acts such as avoiding eye contact or rehearsing sentences to prevent a feared outcome.

The four treatment components have the same content throughout all conditions but are slightly changed to make sense when combined in a particular treatment condition. Short, specific psychoeducation is also given as an introduction to each component (e.g., an explanation about the relationship between cognition and emotions in the cognitive restructuring component). Moreover, all participants, independent of the condition, get an introduction module at the beginning and a conclusion module at the end. The introduction module gives an overview of the program and informs the participants about how they can work with it. As a motivational strategy, participants are asked to list their personal goals with the treatment and the expected life changes after overcoming the symptoms of social anxiety. The introduction module has the same content for all conditions. In the conclusion modules, participants are provided with a summary of the steps they should follow and repeat after the program termination. They are also asked to summarize the exercises, thoughts, and behaviors that helped them cope with relapses and were generally perceived as the most helpful. We wrote sixteen different conclusion modules since the summary and recommended repetition are different for every condition.

Shyne can be accessed through a secure website from various devices such as PCs, tablets and smartphones, with each participant having a password-protected account. The program will automatically record participants' usage of Shyne, allowing for an automated measure of treatment adherence and treatment dosage.

### Minimal guidance

2.5

The role of the guides is to reinforce independent program use and keep up the participants' motivation and adherence. Participants will also have the opportunity to send questions to their assigned guide throughout the program if they have difficulties with the program. As in other studies (Berger et al., 2009, Berger et al., 2011; Schulz et al., 2016; Stolz et al., 2018), the guides monitor the progress of the participants in the program and contact them via a secured text-based messaging system once a week to provide feedback and encourage further engagement. In case of non-adherence, the guides will remind the participants of the importance of reading the material and doing the exercises proposed by Shyne. Guides will also encourage repetition, especially in conditions with fewer components, to ensure dosage equivalence across all conditions. Minimal guidance will be provided by advanced master's students in clinical psychology and psychotherapy. Guides will be randomly assigned to participants across the conditions.

Training and weekly supervision of the master students for the diagnostic interview and guidance will be provided by the first, second and last author (two licensed psychotherapists and experienced in internet-based guided self-help treatments, and a PhD student in clinical psychology). In the supervision, the chats between participants and guides are reviewed, and it is made sure that guidance is being kept at a minimal level.

### Procedures

2.6

The study procedures have been approved by the Ethics Committee of the Canton Bern (KEK Bern 2020-02952) and were registered on clinicaltrials.gov (NCT04879641). After receiving the study information and signing the informed consent, the candidates will be screened for eligibility with self-report measures. Potential participants who fulfill the inclusion criteria will be interviewed by telephone to ascertain whether they meet the criteria for SAD. After checking the inclusion criteria, the eligible participants will be randomized with equal probability to one of the 16 treatment conditions. A permuted block randomization schedule will be created using the *blockrand* package in R (Snow, 2020). The random allocation will be concealed to the investigators and done by the in-built randomization module in the REDCap software (Harris et al., 2009, Harris et al., 2019). Assessments of the primary and secondary outcomes and hypothesized mediators are taken at (1) baseline (pre-treatment), (2) at four weeks after randomization (mid-treatment), (3) eight weeks after randomization (post-treatment), and (4) at six months after randomization (follow-up).

As shown in Table 1, all conditions contain at least one component of ICBT for SAD, except for condition number 1, which is a wait-list control group. For ethical reasons, participants randomly assigned to the wait-list control group will receive the full treatment (i.e., condition 16) after the post-assessment. Participants randomized to one of the active treatment conditions can use the full treatment after the follow-up assessment (Fig. 1).

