##### M.I.N.I. International Neuropsychiatric Interview for DSM-IV 6.0.0 (M.I.N.I.; Sheehan et al., 1998; German version: Ackenheil et al., 1999)

2.7.2.1

M.I.N.I. is a brief structured diagnostic interview for assessing psychiatric diagnosis based on the DSM-IV. The specificity of the M.I.N.I was reported as suitable for all diagnoses (ranging from 0.72 to 0.97; 0.81 for SAD; Sheehan et al., 1997). In our study, the M.I.N.I. interview will be administered via telephone. It will assess depressive episodes, suicidality, manic and hypomanic episodes, panic disorder, agoraphobia, SAD, obsessive-compulsive disorder, post-traumatic stress disorder, substance abuse and addiction, psychosis, anorexia and bulimia nervosa and generalized anxiety disorder. The diagnosis of SAD will serve as an eligibility criterion and a secondary outcome measure (an absence of diagnosis at post-treatment and follow-up suggesting treatment success).

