### Statistical analyses

2.9

Reporting will follow CONSORT E-Health standards (Eysenbach and Consort-Ehealth Group, 2011). The primary outcome is the change in the composite score of SPS & SIAS from baseline to eight weeks (post-treatment). The analyses are carried out on the basis of the intention-to-treat approach (ITT; i.e., using all randomized participants). Our primary interest is in testing the main effects and interactions. For that, we will use linear mixed models repeated measures analysis of variance (ANOVA). This approach uses all available data on each subject and does not require the imputation of missing values but estimates parameters about missing values. Furthermore, mixed models account for the correlation between the repeated measurements. Main effects and interactions are calculated based on aggregates across experimental conditions. The levels of the factors will be represented numerically by −1 (absence of a component in a condition) and +1 (presence of a component in a condition), as recommended by Collins (2018). Significance testing of dichotomous data such as diagnostic status will be conducted with chi-square tests. Sensitivity analysis will be conducted to analyze the impact of dropouts on our results.

We will test mediation of the hypothesized change mechanisms (i.e., knowledge gain of SAD, decrease of dysfunctional social cognitions, decrease of self-focused attention, decrease of avoidance and safety behaviors) of the effect of the treatment components on primary and secondary outcomes (see Fig. 2 above). We will test mediation of the hypothesized change mechanisms by using an approach that allows multiple mediators in one model, as set out by Kraemer et al. (2002).

In addition, we will explore potential moderation of the treatment components by various measured variables (i.e., age, gender, country of origin, nationality, country of parents, mother tongue, relationship status, educational level, employment status, presence of comorbid disorder, use of medication, the severity of SAD). For the analysis of potential moderators, factorial ANOVA and multiple regression analysis will be used.

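### At the 6-month follow-up the wait-list group has been offered the full programme, yet the stated rules still count it as untreated on all four factors, which biases follow-up component effects (not the 8-week primary endpoint)

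*Protocol article*

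**What the plan says.** On treatment after week 8, the Procedures section states that "participants randomly assigned to the wait-list control group will receive the full treatment (i.e., condition 16) after the post-assessment". The note to Table 1 is softer: "participants randomized to condition 1 will be offered treatment after eight weeks". The other 15 conditions do not change before follow-up: "Participants randomized to one of the active treatment conditions can use the full treatment after the follow-up assessment".

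On measurement, Procedures places the last assessment of outcomes and hypothesized mediators "at six months after randomization (follow-up"). Table 2 lists follow-up for every instrument except the satisfaction questionnaire and makes no exception for condition 1. The M.I.N.I. section makes diagnosis at that visit a secondary outcome, with "an absence of diagnosis at post-treatment and follow-up suggesting treatment success".

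On analysis, the Study design section says "Each estimation of the main effects and interactions is based on all the conditions and, therefore, on all participants". The Statistical analyses section prescribes intention-to-treat on all randomized participants, says of the mixed model that "This approach uses all available data on each subject", and gives one coding rule, with factor levels "represented numerically by −1 (absence of a component in a condition) and +1 (presence of a component in a condition"). It gives no separate rule for the 6-month data. The limitations in the Discussion cover dosage, spillover and the reliability of the knowledge test, but not this crossover.

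**The concern.** Exactly one of the 16 cells changes exposure between week 8 and month 6, and it goes from no component to all four. Under the stated rules its 6-month data enter as absent on psychoeducation, cognitive restructuring, attention training and exposure alike. The follow-up contrasts then no longer compare component present with component absent, which is how the Study design section defines a main effect.

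What is at stake is the trial's evidence on durability and on synergy at 6 months, for symptoms, secondary outcomes, diagnosis and mediators. Because a single corner cell of the design is displaced, the error does not stay in one effect. It reaches all four main effects and all eleven interactions. It is a bias, so a larger follow-up sample does not reduce it.

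**Working it through.** **Inputs**
- 16 conditions with 29 participants each (Participants); 232 per factor level (Sample size). These reproduce: 464/16 = 29 and 8 × 29 = 232.
- 0.2 SD per component: the smallest relevant effect in the Sample size section, where it refers to pre-to-post change. Using it at 6 months is an assumption.
- Uptake u of the offered programme: not stated. Range shown: 100%, 50%, 25%.
- Further assumptions: component effects add up, persist to 6 months, and give no benefit to those who do not take up the offer. Effects are expressed as benefit, so positive means improvement.

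**Weight of condition 1**
- It is 29/232 = 1/8 of the absent side of every factor.
- For any pair of factors, four conditions are absent on both (4 × 29 = 116), so it is 29/116 = 1/4 of that cell.

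**Bias if the crossover improves its mean by D**
- Main effect = mean(present) − mean(absent), so it shifts by −D/8.
- Two-way interaction, as the difference of differences that the Study design section describes: the absent–absent cell enters with a plus sign, so it shifts by +D/4.
- With four components of 0.2, D = u × 4 × 0.2 = 0.8u.

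| Uptake | D | Main effect (true 0.20) | Two-way interaction (true 0) |
|---|---|---|---|
| 100% | 0.8 | 0.20 − 0.10 = 0.10 | +0.20 |
| 50% | 0.4 | 0.20 − 0.05 = 0.15 | +0.10 |
| 25% | 0.2 | 0.20 − 0.025 = 0.175 | +0.05 |

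Solving the saturated effect-coded model on the 16 cell means at 100% and 50% uptake gives the same results. On the main-effect scale (half the difference of differences) all eleven interactions shift by D/8 in absolute value, the three-way terms in the opposite direction to the two-way and four-way terms.

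**A component with no effect.** With true effects of 0.4, 0.2, 0.2 and 0, D is again 0.8 at full uptake. The null component is estimated at 0 − 0.10 = −0.10, that is, as harmful.

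**Effect on the tests.** Take SD 1, all 464 observed and a two-sided 5% level. The standard error of a contrast is √(4/464) = 0.093. Power for a true main effect of 0.20 is 58%. At full uptake the expected estimate of 0.10 is detected 19% of the time, and each truly null two-way interaction is rejected 19% of the time instead of 5%. At 50% uptake that false-positive rate is about 8%.

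**Check of the remedy**
- A regression on the 15 uncrossed cells returns 0.20 for every main effect when effects are additive.
- Dropping one cell from the balanced design multiplies the variance of a coefficient by 1 + 1/(16 − p), where p is the number of parameters.
  - Main effects only, p = 5: 1.091, standard error up 4.4%.
  - With two-way terms, p = 11: 1.20, up 9.5%.
  - With three-way terms as well, p = 15: 2.0, up 41%.
- The full model needs 16 parameters and cannot be fitted to 15 cells.
- Raw marginal means without condition 1 are still biased. The present mean is 0.20 + 2.4/8 = 0.50 and the absent mean is 2.4/7 = 0.343, so the difference is 0.157 instead of 0.20.

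**The case against.** The strongest defence is that the trial's main question is untouched. The primary outcome is change from baseline to eight weeks, the sample size rests on pre-to-post change, and condition 1 crosses over only after that assessment. This stands in full. A reader might infer that the primary model is contaminated if all four time points are fitted together. The documents do not support that: they do not say the primary test is fitted that way, and with time as a category the week-8 contrast has its own parameters.

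Second, no sentence says outright that condition 1 is coded absent at 6 months. This is correct: it follows from the only coding rule, the intention-to-treat set and the all-conditions statement. The participant-flow figure, which is not available here, might show that condition 1 supplies no follow-up data. The bias would then vanish, but the all-conditions statement could not hold at 6 months. Handling of crossover data is often left to a statistical analysis plan, and its absence alone would be no finding. Here, however, the rules that are given lead to a wrong estimate when followed.

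Third, halved main effects are not a forecast. They need full uptake, additivity and persistence, while the Table 1 note says only that treatment is offered. That stands, and is why a range is shown. It would also be wrong to say that every effect is pulled toward zero: a null component moves away from it.

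Fourth, the as-assigned comparison is a valid intention-to-treat contrast. It is, for a policy of wait-list followed by full treatment. That is not the effect of a component being present versus absent.

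**Conclusion.** The point holds for the 6-month follow-up only. Under the stated rules, every follow-up main effect is shifted down by D/8 and every two-way interaction is shifted toward apparent synergy by D/4. The direction holds whenever the crossover benefits condition 1. The size rests on uptake and persistence, neither of which is given, and on the assumed 0.2 SD additive effects. At full uptake the spurious two-way interaction, as a difference of differences, is numerically as large as the 0.2 that the plan treats as the smallest effect of interest; at 25% uptake the distortion is minor. This should be fixed before follow-up conclusions are drawn. It gives no reason to doubt the 8-week primary analysis or the delayed offer of treatment itself.

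**What to change.** State in the analysis section that, for 6-month component effects on symptoms, secondary outcomes, diagnosis and mediators:

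- condition 1's data after the crossover are left out;
- main effects and two-way interactions are estimated by a regression model on the other 15 conditions, not by comparing raw marginal means;
- for diagnosis, this means a model for a binary outcome in place of a chi-square test on present-versus-absent margins;
- condition 1 at 6 months is reported descriptively, with its uptake of the programme;
- the as-assigned analysis of all 16 conditions may be kept as a sensitivity analysis, labelled as a contrast involving wait-list then full treatment.

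The cost is wording plus some precision at follow-up. In the linear model, standard errors rise by 4.4% with main effects only, or 9.5% with two-way terms. The price in assumptions should be stated openly: three- and four-way interactions are taken as zero at 6 months. Keeping the three-way terms would raise the main-effect standard error by 41%, and the four-way term cannot be estimated at all. Sample size, treatment delivery and the 8-week analysis need no change.
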